#### Plans to give access to the full protocol, participant-level data, and statistical code {31c}

The full protocol is published as part of our approved IND at ClinicalTrials.gov. Participant-level data will be reported at ClinicalTrials.gov following the completion of the trial.

### Oversight and monitoring

#### Composition of the coordinating center and trial steering committee {5d}

This trial is overseen by a committee of data safety monitors. The roles of individuals within this committee are equal. Data management in this trial is overseen by the University of Rochester Wilmot Cancer Center Data Management team. This trial is also overseen by the Institutional Review Board at the University of Rochester Medical Center, as per the guidelines outlined in the Investigational New Drug approval obtained by the study team.

#### Composition of the data monitoring committee, its role, and reporting structure {21a}

Study investigators will conduct a continuous review of data and subject safety. The investigators will submit annual progress reports of these data to the Wilmot Cancer Center’s Data Safety Monitoring Committee (DSMC) for review. The review will include the number of subjects enrolled, withdrawals, serious adverse events, both expected and unexpected, and responses observed.

The Data Safety Monitoring Committee (DSMC) consists of [name]; [name]; [name]; [name], PhD; [name]; [name], MPH; [name]; [name]; [name]; [name]; [name]; [name]; and [name].

#### Adverse event reporting and harms {22}

Adverse events will be tabulated by treatment, severity, and perceived relationship to the study drug.

For each adverse event, comparisons will be performed among 4AP and placebo regarding the occurrence of at least one event using Prescott’s test [15]. Particular attention will be paid to AEs known to be associated with 4AP in previous studies and to serious AEs.

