### Trial design {8}

This is a single-center double-blind, randomized, placebo-controlled, superiority-designed clinical trial to determine if the use of 4AP can accelerate the return of erectile function to baseline levels. The treatment group will receive the active study drug after surgery for 2 months (60 days), and the placebo group will receive a matching placebo after surgery for 2 months (60 days).

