#### Intervention description {11a}

Subjects will be randomized equally into one of two groups. Both the subject and investigators will be blinded to group assignment.The treatment group (40 subjects) will receive the study drug daily, in two oral doses, taken at least 12 h apart (approximately 8:00 am; 8:00 pm), starting on the day after surgery with the approximately 8:00 am dose. The treatment group will continue at this same dose and daily dosing regimen for 2 months (60 days).The placebo group (40 subjects) will receive a placebo daily, in two oral doses, taken at least 12 h apart (approximately 8:00 am; 8:00 pm), starting on the day after surgery with the approximately 8:00 am dose. The placebo group will continue at this same dose and daily dosing regimen for 2 months (60 days).

The following are the dosing instructions:Dosing schedule = 1 capsule in the morning and another capsule 12 h later (approximately 8:00 am; 8:00 pm).Dosing to begin the day after surgery with the 8:00 am dose.Subjects will not take more than two capsules in a 24-h period.Subjects will take the capsules whole. They will not break, crush, chew, or dissolve capsules before swallowing. The subjects will be told that the medication is released slowly over time, and if the tablet is broken, the medicine may be released too fast which can raise the chance of having a seizure.The study drug can be taken with or without food.If a dose is missed, they should not make up the missed dose; however, subjects may take the dose within 1 h of the scheduled time. They will be told not to take two doses at the same time but to take the next dose at the regular scheduled time.If the subject is unable to take the study medication due to surgical complications (such as ileus), the doses will be skipped and the subject will resume the study medication once able to take other medications by mouth. The subject will not make up the missed doses.Subjects will be reminded not to take the study drug together with other aminopyridine medications, including compounded 4AP (sometimes called 4-aminopyridine or fampridine).

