## Sample size {14}

The primary outcome is return to baseline ability to achieve and maintain erection as measured by Item of the Abridged International Index of Erectile Function (IIEF-5) by 12 weeks after surgery. Suppose at the conclusion of the follow-up period, the rates of returning to the baseline ability in the treatment and control groups are 70% and 30%, respectively. Pearson’s chi-square test indicates that a sample size of 56 (with 28 individuals in each group) achieves 90% power to detect the intended difference of 40% (at a significance level of 0.05). Accounting for an estimated dropout rate of 30%, we plan to recruit 40 subjects in each group.

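### The test named for comparing adverse events, Prescott's test, is a two-period crossover test and cannot be computed in this parallel-group trial

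*Protocol article*

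**What the plan says.** The section Adverse event reporting and harms {22} first plans a tabulation of adverse events by treatment, severity and perceived relationship to study drug. It then adds a test: for each adverse event, "comparisons will be performed among 4AP and placebo regarding the occurrence of at least one event using Prescott’s test", citing reference [15]. No other test is named in that section.

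The design is described elsewhere. Trial design {8} says "This is a single-center double-blind, randomized, placebo-controlled, superiority-designed clinical trial". On the two arms, it says of one that "The treatment group will receive the active study drug after surgery for 2 months (60 days" and of the other that "the placebo group will receive a matching placebo after surgery for 2 months (60 days". Intervention description {11a} says "Subjects will be randomized equally into one of two groups", with 40 men planned in each, and of the active arm that "The treatment group will continue at this same dose and daily dosing regimen for 2 months (60 days". The placebo arm has the same instruction. The article mentions no switch of treatment, washout, second treatment period or treatment sequence.

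Separately, item (1), Descriptive statistics, in the section on statistical methods {20a} names Pearson's chi-square or Fisher's exact test for comparing the two groups on categorical variables.

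**The concern.** A crossover test is prescribed for a trial in which nobody crosses over. This is a positive choice of method and not a detail left to a later document, so an analysis plan that followed the protocol would inherit it.

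What is at stake is the only inferential method that the safety section names. Safety matters for this drug: a history of seizures is an exclusion, men are warned of a raised chance of seizure if the product is broken, and a seizure on treatment leads to withdrawal. The safety section itself promises particular attention to events already linked to 4AP. The analyst will have to replace the stated test, and the protocol should say with what.

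**Working it through.** The article gives no figure for the adverse event comparison, so there is none to reproduce. The check sets what the test needs beside what the design supplies.

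**What Prescott's test needs.** Two treatments, A and B, given in two orders (AB and BA), and a yes/no outcome for every subject in each period. Score each subject by d = y1 − y2, where y1 and y2 are the outcomes (0 or 1) in periods 1 and 2. The test is run on this table:

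| Sequence | Event in period 1 only (d = 1) | Same in both (d = 0) | Event in period 2 only (d = −1) |
|---|---|---|---|
| AB | count | count | count |
| BA | count | count | count |

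**What the trial supplies.**

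| Requirement | This trial | Source |
|---|---|---|
| Two treatments per subject | One: 4AP or placebo | Trial design {8} |
| Two treatment periods | One course of 60 days | Trial design {8}; Intervention description {11a} |
| A randomized order of treatments | None; men are allocated 1:1 to a group | Intervention description {11a} |
| y1 and y2 for each subject | One yes/no outcome per adverse event | Adverse event reporting and harms {22} |

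Subjects with outcomes under both treatments: 0 of 40 + 40 = 80. With no y2 there is no d, with no sequence there are no rows, and the statistic is undefined for every adverse event.

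**Could the months after treatment serve as period 2?** No. Neither group moves to the other's treatment, so the rows would be 4AP then nothing and placebo then nothing. That is not the planned comparison of 4AP with placebo, and the quoted sentence does not split events by period.

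**What the data do form.** An ordinary 2 × 2 table of group by at least one event (yes or no), which Fisher's exact test handles directly.

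**How the replacement behaves at 40 per group.** These figures describe Fisher's test (two-sided) and the trial's size. They do not measure the cost of naming the wrong test, and the event counts and rates are assumptions.

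- 5/40 v 0/40: p = 2 × C(40,5)/C(80,5) = 0.055.
- 6/40 v 0/40: p = 2 × C(40,6)/C(80,6) = 0.026.
- 8/40 v 2/40: p = 0.087.
- Exact power at two-sided 0.05: 41% for true rates of 20% v 5%, 53% for 30% v 10%, and 85% for 40% v 10%.

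A p-value alone will therefore often be uninformative for uncommon events, which is why an interval is worth adding.

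**The case against.** The case for leaving the text alone has three parts.

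1. The general methods already name chi-square or Fisher's exact test for categorical comparisons of the two groups, and having at least one event is such a variable. Much of this stands. A reader might infer that the substitute test would be picked freely once the data are seen. The article does not support that, because the natural replacement is its own published method. The cover is not complete, though: that item refers to covariates and outcomes, adverse events are not among the listed outcomes, and the safety section gives its own, different instruction.

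2. A reader might infer that the safety evaluation as a whole fails. It does not. The tabulation can be done in full. Oversight rests on the safety committee's review of withdrawals and serious adverse events, and on withdrawal rules for individual men. No interim analysis is planned, and no stopping rule or efficacy conclusion in the article depends on an adverse event p-value.

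3. The point depends on what Prescott's test is, and the reference list is not shown. This does not rescue the text: the argument needs only the definition of the named method. It does limit what can be said about citation [15]. The methods section also cites it, with [14], for the weighted GEE, so it may be a numbering slip in one of the two places. That is a reason to check it, not evidence of what it contains.

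**Conclusion.** The point holds in limited form. The named test does not fit the design, and the inferential comparison fails for every adverse event, with 0 of 80 planned men contributing usable data. Tabulation, primary and secondary efficacy analyses and sample size are untouched.

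This rests on two things: that Prescott's test means the crossover test of that name, and that the trial is parallel-group. The article does not use the word parallel in describing the design, but one treatment and one course per man leave no other reading.

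It is tempting to call this critical because the drug carries a seizure warning. The article does not bear that out: the descriptive safety reporting survives, a suitable test is already named elsewhere, and per-event tests at 40 per group have modest power in any case. It should be fixed, but it does not threaten the trial's conclusions. A statistical analysis plan not shown here may already have corrected it; the protocol text would still need to agree.

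**What to change.** In Adverse event reporting and harms {22}, replace the reference to Prescott's test with wording such as: for each adverse event, the proportion of men with at least one event will be compared between 4AP and placebo using Fisher's exact test. Preferably add that the risk difference will be reported with a 95% confidence interval.

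Check citation [15] in both places where it appears, and keep it only where it supports the method named.

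The cost is one sentence and one citation check, best made before the allocation is unblinded for analysis. Data collection and sample size do not change. The definition of the safety analysis set can stay with the full protocol or statistical analysis plan; correcting this sentence does not require it.

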#### Frequency and plans for auditing trial conduct {23}

The procedures for auditing trials conducted at the University of Rochester include yearly, as well as interspersed, sporadic audits conducted by the University of Rochester Institutional Review Board-governed by a trial audit team. This process is independent from the investigators and the sponsor.

#### Plans for communicating important protocol amendments to relevant parties (e.g., trial participants, ethical committees) {25}

All protocol amendments are reviewed by the URMC IRB. Any amendments that would alter a participant’s eligibility or study protocol would be reported directly.

#### Dissemination plans {31a}

The authors intend to collaborate and disseminate the results of this study via publication in the peer review literature. Deidentified results databases will be attached to the publication for independent review.

## Discussion

This study is critical as it provides an important opportunity to look at TPNI in subjects undergoing NSRP. Currently, clinical research on TPNI is challenging, as many who present with TPNI have great variability in the injuries sustained. TPNI can be debilitating, and currently, there are no proven therapies to help recover function. RP is the standard surgical treatment for localized PCa, which includes surgical removal of the prostate while preserving the neurovascular bundle on the posterolateral aspects of the prostate. The surgical dissection performed using a standard approach, although resulting in consistent tension, results in limited variability with postoperative ED and UI. Thus, this procedure would be ideal to investigate a drug that may enhance recovery of controlled TPNI.

Critically, we are limiting the use of PDE5 inhibitors for 3 months after surgery. Often, men have significant ED 3-months after surgery. While PDE5 inhibitors have been shown to improve the ability to achieve erections after RP, they have not been shown to help improve recovery of erectile function. Limiting the use of PDE5 inhibitors for 3 months prevents confounding that would be difficult to interpret without much larger studies. This is an important consideration for those creating trials looking at TPNI in men who undergo NSRP. However, if this study is successful, 4AP would likely become the standard of care and future studies would need to look at whether immediate use of PDE5 inhibitors help enhance recovery of erectile function when taken in combination with 4AP.

This study design will hopefully provide a model to help advance the study of TPNI. Men undergoing NSRP, as well as many others who sustain TPNI from other causes, could benefit from identifying clinically useful medications that help with nerve regeneration after injury.

## Trial status

The currently approved protocol is version date 05/03/2023. Enrollment for this trial began in December 2019. Recruitment is estimated to be completed by mid-2023.

## Data Availability

Deidentified data associated with this trial will be openly available to investigators at the conclusion of the analysis.

## Abbreviations

4AP: 4-Aminopyridine
TPNI: Traumatic peripheral nerve injury
URMC: University of Rochester Medical Center
RRP: Radical retro-pubic prostatectomy
MS: Multiple sclerosis
IR: Immediate release
FDA: Food and Drug Administration
CPK: Creatinine phosphokinase
NSRP: Nerve-sparing radical prostatectomy
PSA: Prostate-specific antigen
IIEF 5: International Index of Erectile Function
ED: Erectile dysfunction
DSMC: Data Safety Monitoring Committee
AE: Adverse event
SAE: Serious adverse event
PDE5: Phosphodiesterase type 5
M-ISI: Michigan Incontinence Symptom Index
IDS: Investigational Drug Service
MAR: Missing at random
GEE: Generalized estimation equation
GFR: Glomerular filtration rate
CBC: Complete blood count
BMP: Basic metabolic panel
